#### Strategies to enhance the exercise experience of the participants

##### Self-efficacy 

Every participant will have an exercise booklet, pedometer, and activity diary to remind them to be active daily. For the TE group, the assistants will conduct home visits to help the participants to set up their tablets and inspect their home environment. Colourful notecards will be provided to remind the participants of the procedures for attending the online class. Exercise videos will be uploaded to social media so that the participants can follow them during the maintenance phase.

##### Self-confidence

All classes of TE and CB will be led by the same instructor, aged 66, who is experienced in teaching older people. He understands the needs of older people and acts as a role model for the participants. The class size will be between 9 and 10 for both TE and CB, which can promote better interaction and allow the instructor to become familiar with all of them. The first week will allow the participants to get used to the movements. The instructor will correct their movement, assess every participant’s performance and encourage them to complete the exercise or progress to a higher level. The level of exercise will be tailored for all the participants so that they will gain confidence in the completion of the prescribed exercises. The instructor will commend the participants for their effort in performing the prescribed exercises regularly during each lesson. Our team will encourage the participants to be active during the intervention and maintenance phases through regular phone calls or text messages. We will set up an easily achievable target for the participants such as walking 500 steps more for the following week.

##### Empowerment 

Ten minutes will be reserved in each lesson for the participants to express their comments on the exercises and request the exercises that they want. They can discuss with the instructor their performance and whether they can proceed to the next level. The research team will organize a maintenance workshop to present the exercise guidelines, exercise booklet and videos for all the participants to maintain their exercise habits after the 3-month exercise classes. Some reliable web resources will also be recommended to the participants. They will also be advised to participate in exercise courses provided by other community centres.

### Outcome measures

#### Primary outcomes

Trained and blinded assessors will conduct all outcome assessments.

The primary outcomes are the change in muscular strength and physical function among older people compared with different time points, i.e. at the baseline, and after 3, 6 and 12 months. The outcomes include risk of falls (Chinese version of Fall Efficacy Scale-International) and fall incidence, right-hand and left-hand grip strength, 6-meter walk test, SARC-CalF, Timed Up and Go test (TUG), Berg Balance Scale (BBS), functional reach test, skeletal muscle mass and fat mass.

Chinese version of Fall Efficacy Scale-International: This is a validated measurement of fall efficacy with 16 questions regarding confidence of fall prevention at different situations on a four-point scale ranging from “not at all concerned” to “very concerned”. The score ranges from 16 to 64 and a lower score indicates a low fear of falling [35]. A perceived fear of falling is defined as points ≥ 20 [36].History of falls and fall incidence: A fall is defined as “an unexpected event in which the participant comes to rest on the ground, floor, or lower level, with or without injury” [37]. The history of falls including number, circumstance and severity in the previous 12 months will be assessed at the baseline [17]. The participants will be required to record their fall incidence prospectively in their diaries. The project assistant will also contact the participants regularly to ensure that they record the correct information.Right-hand and left-hand grip strength: This measurement will be performed by using a hand dynamometer (Takei Scientific Instruments Co. Ltd, Tokyo, Japan). The participants will be instructed to stand with their elbow extended and squeeze the dynamometer as hard as they can. Three attempts for both hands will be allowed and the mean of three scores will be counted [16].6-metre walk test: This is the test to assess the gait speed of the participants. The participants will be asked to walk as fast as possible without running for 10 m, which comprises a 2-metre approach, 6 m for time measurement and 2 m beyond the measurement. The units of this measurement are in seconds and will be divided by 6 to calculate the gait speed in m/s. Two attempts will be allowed and the mean of two scores will be counted [17].SARC-CalF: This is used to screen sarcopenia. It consists of six components namely strength, assistance in walking, rising from a chair, climbing stairs, falls and calf circumference [38, 39]. According to the Asian Working Group for Sarcopenia 2019 [27], diagnosis of possible sarcopenia includes SARC-CalF ≥ 11, handgrip strength (M:<28 kg, F < 18 kg) and 6-metre walk test < 1.0 m/s.Timed Up and Go Test: This is a test of functional lower-limb mobility. The participants will be seated with arms resting on the armrests. They will be asked to walk for 3 m, return to the chair, and sit down again. The time will be counted from standing to sitting back on the chair. Three attempts will be allowed and the mean of three scores will be counted [16].Berg Balance Scale score: This is a valid and reliable scale consisting of 14 static and dynamic balance activities. The score of each activity ranges from 0 to 4 and the total score ranges from 0 to 56 [40].Functional Reach Test: This test is used to assess dynamic bilateral stance balance. A metre ruler is fixed on the wall at participants’ shoulder height and the participants will be asked to stand next to but not touching the wall. The arm near the wall needs to be raised at 90° flexion and the third finger will be the initial position along the metre ruler. The participants will be asked to reach as far as possible without taking a step, bending their knees or falling over. The end position on the ruler will be marked. Three attempts will be allowed and the mean of three scores will be counted [17].Skeletal muscle mass and fat mass: The participants will be asked to dress in light clothing, hold the handgrips and stand still barefoot on a bioimpedance analyzer (Inbody 230, Biospace Co., Ltd, Seoul, Korea) after overnight fasting. The InBody 230 is a segmental impedance device which uses a tetrapolar 8-point tactile electrode method and two different frequencies (2 and 100 kHz). Fat mass, fat-free mass, percentage body fat and appendicular muscle mass (muscle mass of both arms and legs) are determined by the manufacturer’s algorithm of InBody 230. The appendicular skeletal muscle mass index (ASMI), expressed in kg/m^2^, is calculated by dividing the appendicular muscle mass by the square of height [41].

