## Background

The decline of muscle mass and strength with age will expose older people to a higher risk of sarcopenia and falls. Falls are common among older people. The 1-year prevalence of falls among community-living older people aged 65 years or above with at least one fall is 20% with the fall rate (number of falls per 100 people) 29% in Hong Kong [1]. After the age of 75, the fall rates are even higher [2]. Hip fracture is one of the outcomes of falls among older people and is associated with rehospitalization and increases in hospital stay and mortality rates [3, 4]. Sarcopenia is one of the main reasons of disability, falls and hip fractures in older people and it is a challenge in regard to healthy ageing [5]. To reduce the prevalence and incidence of falls and sarcopenia among older people, exercise training is found to have positive effects on balance, muscle mass and strength, as well as physical functioning [6, 7]. Nevertheless, older people are less likely to participate in fall prevention programmes with exercise classes in Hong Kong because frail older people may not be confident to leave their home and join a programme in the community [8]. Thus, it is necessary to find feasible alternatives to encourage and facilitate older people to develop regular exercise habits.

Telehealth refers to the remote delivery of health care services such as clinic appointments and exercise training (tele-exercise), using information and communication technologies (ICT) where the provider and service recipient are in different physical locations [9]. Occupational and physical therapy practitioners increasingly use tele-exercise to enable real-time interactions between instructors and community-dwelling older people in order to save money and waiting time [10, 11]. Promoting an online home-based exercise programme for older people can encourage them to engage in regular physical activity and increase their exercise adherence even when remaining at home. Tele-exercise was particularly important when people needed to adhere to social distancing during the pandemic.

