### Eligibility criteria

The target group of this research is the community-dwelling older people with possible sarcopenia or at risk of falls in Hong Kong. The inclusion criteria and the exclusion criteria are listed in Table 1. The diagnosis of possible sarcopenia is based on the recommendation of the Asian Working Group for Sarcopenia 2019 (AWGS) [27] to assess the SARC-CalF scores, muscle strength and physical performance. The perceived fear of falls is measured by the Chinese version of Fall Efficacy Scale-International (FES-I). The Mini-Mental State Examination (MMSE) determines if participants show signs of cognitive impairment. Medical clearance will be performed according to the guidelines of the American College of Sports Medicine (ACSM).

**Table 1 Tab1:** Inclusion and exclusion criteria

Inclusion criteria	Exclusion criteria
• permanent residents of Hong Kong • aged 65 years or above living independently at home • diagnosed with possible sarcopenia and/or having had either a fall in the past year or fear of falling with a score of ≥ 20 points on FES-I • able to speak and listen to Cantonese • able to walk without mobility aids in their home	• diagnosed with dementia or cognitive impairment, Mini-Mental State (MMSE) < 25 • severe vision impairments that do not permit the use of a tablet, reading of the exercise booklet, and completing the activity diaries • unable to pass the preparticipation Health Screening of the ACSM and the subsequent medical clearance • regular physical activities in the past 6 months based on the definition of WHO [28]

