### Sample size calculation

In Hong Kong, there are 1,322,000 residents who are aged 65 years or above [29] and it is estimated that 118,980 of them suffer from sarcopenia (prevalence is 9% for those aged 65 or above [30, 31] and 264,400 of them have had at least one fall in the past year [1]. Calculations were performed using G*Power software and an assumed effect size of 0.367 based on a previous study by Benavent-Caballer et al. [32] on the Time Up and Go Test. Considering a 95% confidence level, a power of 80%, and 20% attrition rate (including mortality) [33], a sample size of at least 92 are required.

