### Randomization and blinding

After the screening phase, ten community centres will be coded and then randomized such that a similar number of centres will be allocated to either the tele-exercise group (TE) or community-based group (CB) in a concealed, blinded fashion to minimize cross-over contamination between the groups. An independent assistant will oversee the randomization procedures and allocation sequence. Around ten participants will be recruited from each centre. The assessments will be performed by trained outcome assessors who will be blinded to the group assignments. It is impossible to blind the participants in the training mode. However, they cannot communicate with other groups of participants because they are recruited from different locations. The instructors and researchers will not be blinded and will be asked to refrain from discussing the group assignments of the participants with the outcome assessors.

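### Fall incidence is a primary outcome, but the trial is sized on Timed Up and Go: only a large difference in falls could be shown, and similar counts cannot establish comparability

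*Protocol article*

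**What the plan says.** Under Outcome measures, Primary outcomes, the protocol article lists about ten measures with equal standing. One entry reads: "The outcomes include risk of falls (Chinese version of Fall Efficacy Scale-International) and fall incidence". Falls are recorded in diaries for 12 months (Interventions; Primary outcomes).

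The Sample size calculation takes an effect size of 0.367 from an earlier study "on the Time Up and Go Test", with 95% confidence, 80% power and 20% attrition, and concludes that "a sample size of at least 92 are required". It gives no expected number of falls and no power for falls.

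The only fall rate in the document is in the Background, for community-living people aged 65 or over: "at least one fall is 20% with the fall rate (number of falls per 100 people) 29% in Hong Kong". The same section adds: "After the age of 75, the fall rates are even higher". The trial population is selected for risk; Table 1 requires people "diagnosed with possible sarcopenia and/or having had either a fall in the past year or fear of falling".

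The hypothesis at the end of the Background is that TE matches traditional programmes, without a margin. The Statistical analysis section assigns a two-way repeated measures ANOVA at 0.05 to every outcome and names no term for centre. Yet Randomization and blinding allocates ten community centres, not individuals, to TE or CB.

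**The concern.** Falls are rare events in a trial of 92 people. A comparison of rare counts can miss a difference that matters, and a hypothesis of comparability makes that more serious than usual: a non-significant p-value points the way the investigators hope. The exercise programme is a fall-prevention programme, so readers will look for the falls result. Because falls are listed as primary and no margin or precision is stated, a null comparison on a few dozen events could be reported as a primary finding in favour of TE while still allowing a materially higher fall rate.

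The prescribed analysis adds to this. Repeated measures ANOVA on a sparse, skewed count does not give a rate ratio, and a model without centre ignores the unit that was randomised.

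**Working it through.** **The plan's own figure.** The protocol gives no figure for falls to reproduce. Its 92 does not follow from the stated inputs on two plain readings. With 0.367 as a standardised mean difference, a two-sided two-sample t-test needs 236 in total (295 with attrition). With 0.367 as Cohen's f for two groups, it needs 61 (77 with attrition). That is a separate matter; here 92 is used only as the enrolment target.

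**Inputs.**
- 92 participants, so 46 per arm if equal (Sample size calculation; Randomization and blinding).
- 0.29 falls per person-year, general population aged 65 or over (Background).
- 0.58 per person-year: an assumption, twice that rate, because the protocol gives none for an at-risk group.

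**Expected falls per arm in 12 months.**
- Base rate: 46 × 0.29 = 13.3
- Doubled rate: 46 × 0.58 = 26.7
- Base rate after 20% attrition, completers only: 36.8 × 0.29 = 10.7

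**95% interval for the TE:CB rate ratio if the counts are equal**, exp(±1.96 × √(2/E)), where E is the falls per arm:
- E = 13.3: √(2/13.3) = 0.387, interval 0.47 to 2.14
- E = 26.7: √(2/26.7) = 0.274, interval 0.58 to 1.71
- E = 10.7: interval 0.43 to 2.34
- E = 46 (an assumed one fall per person-year): interval 0.66 to 1.50

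**Power**, Wald test on the log rate ratio, two-sided 5%, SE = √(1/E + 1/(R × E)) for true ratio R:
- R = 2, E = 13.3: SE = 0.335; 0.693/0.335 = 2.07; power 54%
- R = 2, E = 26.7: SE = 0.237; 0.693/0.237 = 2.92; power 83%
- R = 1.5: power 21% at the base rate and 37% at the doubled rate

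**Observed split needed.** With 27 falls in total (base rate), the most even split with exact p < 0.05 is 20 v 7, a ratio of about 2.9. With 53 falls (doubled rate) it is 35 v 18, about 1.9.

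**Overdispersion and centre.** Neither is quantified in the document, so these values are assumptions. At 13.3 falls per arm, a variance factor of 2 for repeat fallers widens 0.47–2.14 to 0.34–2.92. Adding an intraclass correlation of 0.05 with 92/10 = 9.2 people per centre (design effect 1 + 8.2 × 0.05 = 1.41) gives 0.28–3.58. At the doubled rate, a variance factor of 2 gives √(2 × 2/26.7) = 0.387, which brings the interval back to 0.47–2.14.

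**Scale.** Purely as illustration, ruling out a ratio of 1.5 with 80% power (one-sided 2.5%) takes 2 × (2.80/0.405)² ≈ 95 falls per arm, or about 330 people per arm at 0.29.

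**The case against.** The strongest reply is that 29 per 100 is a background figure, not a planning rate. The trial enrols people with possible sarcopenia, a recent fall or fear of falling, so 13 falls per arm is probably low. That stands, and it is why the doubled rate is shown beside it. It narrows the interval but does not rescue comparability: even at an assumed one fall per person-year, equal counts leave ratios up to 1.50.

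A reader might infer that no falls result could support or refute the hypothesis. The figures do not bear that out: a 20 v 7 split would be significant before allowing for clustering, and power for a true doubling is 54% to 83% over the two rates. A large excess in TE could therefore refute comparability. Nor is a null result always compatible with doubling or halving: under a plain Poisson model, 0.58–1.71 excludes both.

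A reader might also infer that the investigators intend to report a null falls result as equal prevention. Nothing in the document says so. The general definition of the primary outcomes concerns muscular strength and physical function, and the stated purposes are physical functioning and adherence. The risk comes from the combination of primary status, a comparability hypothesis and no margin.

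Two further points have some force. The Sample size calculation already names Timed Up and Go, but it does not say that the power does not extend to the other primary outcomes. A statistical analysis plan that is not shown could hold a count model, but the protocol states ANOVA for all outcomes, and no model can supply more falls.

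**Conclusion.** The point holds in a limited form. Fall incidence is a primary outcome that the sample size does not address. At the general-population rate, about 13 falls per arm are expected in 12 months, and equal counts leave the TE:CB ratio anywhere from about 0.47 to 2.14; at an assumed doubled rate, about 0.58 to 1.71. Only a large difference could be shown, and similar counts cannot establish that TE matches face-to-face classes for falls.

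The intervals and power assume 46 per arm, full 12-month follow-up, Poisson counts and independence between people. Attrition, repeat fallers and allocation by centre would normally make the comparison less precise. The conclusion does not depend on how 92 was derived. The figures do not support a claim that the falls comparison is uninformative in both directions.

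**What to change.** 1. **Statistical analysis:** exempt fall incidence from the repeated measures ANOVA. Report the 12-month TE:CB fall rate ratio with a 95% interval that allows for overdispersion and for centre, the unit randomised. A negative binomial model with follow-up time as offset, and a small-sample allowance for only ten centres, would be one way.
2. **Statistical analysis:** state that a non-significant falls result will not be described as equal fall prevention.
3. **Sample size calculation:** state that the 92 and its 80% power refer to Timed Up and Go only.
4. **Primary outcomes:** label fall incidence as an outcome the trial is not powered for.

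Moving falls to the secondary outcomes is optional. Trial Status shows that two CB groups have finished the intervention and three more groups are in it, and the researchers are not blinded. Such a move would need a documented, dated amendment made without sight of outcome data by arm. It would also need a matching change to Secondary outcomes, which is confined to participants' experience.

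The cost of items 1 to 4 is protocol wording and one different model; no extra participants, visits or data are needed. The downside is a more cautious falls conclusion.

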#### Maintenance phase

After 3 months of training, a workshop will be arranged to remind the participants to maintain the exercise habit and achieve a daily step count of > 10,000 steps or increase their step count by 3,500 every three months until they reach 10,000 steps per day. The exercise booklets of our exercise programme will be distributed to all participants. The exercise videos will be sent to them via WhatsApp, or presented to them in a way that they can be easily accessed. They will be reminded by phone at least twice per month to record their exercise and step count in the diary provided.

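### Change in falls from baseline sets a recalled 12-month history, in people partly selected for having fallen, against diary counts over shorter windows, so it cannot be read as an effect

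*Protocol article*

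**What the plan says.** Under Outcome measures, Primary outcomes, the article states: "The primary outcomes are the change in muscular strength and physical function among older people compared with different time points". The time points are baseline and months 3, 6 and 12, and fall incidence is on the list of measures. The Baseline assessment section also lists fall incidence among the measures taken before the intervention.

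The falls item in the same section gives two sources. For baseline: "The history of falls including number, circumstance and severity in the previous 12 months will be assessed at the baseline". For follow-up: "The participants will be required to record their fall incidence prospectively in their diaries". The Interventions section asks for this recording over 12 months.

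Table 1 (Eligibility criteria) admits people "diagnosed with possible sarcopenia and/or having had either a fall in the past year or fear of falling", the last defined by an FES-I score of at least 20. A past fall is thus one of several alternative ways in.

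The Statistical analysis section applies a two-way repeated measures ANOVA to all outcome measures, with group and the group-by-time interaction. Falls are not set apart. Randomization and blinding allocates ten community centres, not individuals.

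**The concern.** Three things change between the baseline value and the later values of this one outcome.

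- **Selection.** Some participants are enrolled because they fell in the past year. Their baseline count is high partly by chance and would be expected to drop with no intervention.
- **Counting method.** Recall over a year gives way to a prospective diary. If recall misses falls that a diary catches, the later values rise.
- **Window length.** Twelve months at baseline is followed by 3, 3 and 6 months between visits.

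Both arms exercise, so no untreated arm shows what falls would have done anyway. The hypothesis is that tele-exercise (TE) is as effective as the traditional format (CB). A non-significant interaction beside a drop in both arms would invite the conclusion that both programmes reduce falls, and the data could not support that for this outcome. A baseline measured differently and inflated by selection also enters the group-by-time contrast, where it matters if the arms differ in their share of past-year fallers.

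**Working it through.** The article states no figure for this point, so there is none to reproduce. The size can be gauged from two numbers in its Background section: 20% of community-living older people fall at least once a year, and there are 29 falls per 100 people per year.

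**Model.** Let individual fall rates follow a gamma distribution with mean 0.29 and shape k, and let counts be Poisson given the rate. Setting P(no fall) = (k/(k+0.29))^k = 0.80 gives k = 0.444.

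- Past-year falls among fallers: 0.29/0.20 = 1.45.
- Expected rate next year in those with no past-year fall: k/(k/0.29 + 1) = 0.175.
- Expected rate next year in past-year fallers: (0.29 − 0.80 × 0.175)/0.20 = 0.749 (unrounded inputs).

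**Assumptions not in the document.** The share p of participants with a past-year fall is unstated, as is the completeness of recall. Participants are taken to resemble the general-population fallers and non-fallers of the same age group. If those entering through possible sarcopenia or fear of falling have a rate above 0.175, the drops below are too large.

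**Change from baseline with no treatment effect.** Baseline is 1.45p and follow-up is 0.749p + 0.175(1−p).

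| p | Baseline per year | Follow-up per year | Change, full recall | Change, 80% recall | Raw 3-month vs 12-month count |
|---|---|---|---|---|---|
| 30% | 0.435 | 0.347 | −20% | about 0% | −80% |
| 50% | 0.725 | 0.462 | −36% | −20% | −84% |
| 70% | 1.015 | 0.577 | −43% | −29% | −86% |

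With recall at 70%, the changes are +14%, −9% and −19%. With recall at 90%, they are −11%, −29% and −37%. At p = 20%, the population share, full recall gives 0% and 80% recall gives +25%. Sign as well as size therefore depends on unknowns. Rescaling to a common window removes the last column but not the two before it.

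**Between arms, no effect, balanced.** In 4,000 simulated trials of 92 people (46 per arm, half fallers, individual allocation, full recall), the between-arm difference in change averaged 0.001 falls per year (SE 0.003) and was significant in 5.3%. A test of pooled change from baseline was significant in 74% of the same trials.

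**Between arms, no effect, imbalanced.**

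- 40% fallers: baseline 0.580, follow-up 0.405, change −0.175.
- 60% fallers: baseline 0.870, follow-up 0.519, change −0.351.
- Spurious difference in change: 0.351 − 0.175, about 0.18 falls per year, in favour of the arm with more fallers.
- Follow-up rates alone, without adjustment: 0.519 − 0.405 = 0.114 per year, in favour of the arm with fewer fallers. Fall history is therefore needed as a covariate.

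**The case against.** The strongest reply is that the trial does not rest on before/after change. Its objective is TE compared with CB, the community arm is a positive control, and the named ANOVA terms are group and group by time. Both arms share the entry rule, the recall question and the diary, so the distortion cancels on average. This stands, and the simulation bears it out. A reader might infer that the arm comparison itself is biased by design; the document does not support that. What remains is that the outcome is worded as change over time, and that cancellation needs similar faller shares in the two arms, which ten randomised centres do not assure. The simulation allocated individuals, so it does not test that.

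A second reply is that retrospective history is the only baseline available at enrolment. That is true, and collecting it is no fault. The fault lies in using it as the first value of a repeated outcome.

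A third is that window scaling may be settled in an analysis plan not shown here. That is fair, and its absence is not the point: scaling leaves selection and counting method untouched.

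A reader might also infer that fall reporting must decline after month 3, because the maintenance-phase reminder names only exercise and steps: "They will be reminded by phone at least twice per month to record their exercise and step count in the diary provided". The falls item itself promises fall-record contact: "The project assistant will also contact the participants regularly to ensure that they record the correct information". Nothing says that falls were asked about in class, so no drop in prompting can be computed.

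**Conclusion.** The point holds as one of confounding. Change from baseline in falls mixes any real effect with selection, counting method and window length. With no effect and complete recall, the annualised rate would drop by about 20% to 43% at assumed faller shares of 30% to 70%. Incomplete recall works the other way and, at 30% fallers and 80% recall, cancels the drop. Raw 3-month counts set against the 12-month history would show a spurious drop of 80% to 86% over the same range of shares.

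It would be tempting to call the whole change an artefact. The document does not support that: a past fall is only one alternative entry route, the faller share and recall completeness are unstated, the two distortions oppose each other, and a real change may be mixed in.

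The TE-versus-CB contrast is unbiased on average but exposed to chance imbalance between centres: about 0.18 falls per year for 40% against 60% fallers. These sizes rest on the gamma-Poisson model and on the Background figures applying to the enrolled population.

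**What to change.** In Primary outcomes and Statistical analysis, take falls out of the common repeated measures ANOVA and state that:

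- the fall endpoint is the TE-versus-CB comparison of diary falls after intervention start, analysed as a rate with person-time, for example by a negative binomial model allowing for centre;
- the 12-month fall history is used only as a baseline covariate;
- a within-arm change in falls from baseline will not be reported as an effect.

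The cost is wording in two sections and the loss of a before/after statement on falls that the design cannot support. The data already planned suffice. A new fall question in the phone calls is not advised: Trial Status reports that three CB and two TE groups have already started, so adding one now would change how falls are ascertained mid-trial.

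### As written, the 6-metre walk formula (seconds divided by 6) gives seconds per metre, the reciprocal of the gait speed in m/s that it claims to give

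*Protocol article*

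**What the plan says.** The 6-metre walk is described under Primary outcomes in the protocol article. Its purpose is plain: "This is the test to assess the gait speed of the participants". The course is 10 m long, "which comprises a 2-metre approach, 6 m for time measurement and 2 m beyond the measurement", so the timed distance is 6 m. The conversion rule follows: "The units of this measurement are in seconds and will be divided by 6 to calculate the gait speed in m/s". Two attempts are made and the mean of the two scores is used.

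The result serves two purposes.

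- **Eligibility.** The SARC-CalF entry in the same section says that "diagnosis of possible sarcopenia includes SARC-CalF ≥ 11, handgrip strength (M:<28 kg, F < 18 kg) and 6-metre walk test < 1.0 m/s". The Eligibility criteria section likewise bases possible sarcopenia on an assessment "to assess the SARC-CalF scores, muscle strength and physical performance". Table 1 makes it one of several routes into the trial: "diagnosed with possible sarcopenia and/or having had either a fall in the past year or fear of falling with a score of ≥ 20 points". The score meant there is the FES-I.
- **Outcome.** The 6-metre walk is listed among the primary outcomes, measured at baseline and at 3, 6 and 12 months.

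No other section gives a different formula.

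**The concern.** Dividing a time by a distance does not give a speed. The rule contradicts the unit named in its own sentence, and it runs backwards: the longer a person takes, the higher the value.

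Two things would be at stake if the rule were followed to the letter. The gait-speed component of possible sarcopenia would be met by the wrong side of the 1.0 cut-off. And a participant who became faster would be recorded as having lost speed, so a reader of a results table headed m/s would take the direction of effect the wrong way round.

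The point is live because the trial is under way. The Trial Status section reports two CB groups that have completed the 3-month intervention, and one CB and two TE groups that are in it. Data pass from the assessors' forms to a project assistant for entry, and the analysis is done by an independent statistician. Any of them could reasonably rely on the published rule.

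**Working it through.** **Inputs.** Timed distance 6 m; time t in seconds; cut-off < 1.0 m/s. All are from the Primary outcomes section. The walking times below are illustrative, since the article reports none.

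**Units.** Rule as written: t / 6, in seconds per metre. Speed by definition: 6 / t, in metres per second. Each is the reciprocal of the other, and they agree only at t = 6 s.

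**Classification against the cut-off.**

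| Time (s) | True speed 6/t (m/s) | Rule as written t/6 | Truly < 1.0? | Rule says < 1.0? |
|---|---|---|---|---|
| 4 | 1.50 | 0.67 | no | yes |
| 5 | 1.20 | 0.83 | no | yes |
| 6 | 1.00 | 1.00 | no | no |
| 7.5 | 0.80 | 1.25 | yes | no |
| 8 | 0.75 | 1.33 | yes | no |
| 10 | 0.60 | 1.67 | yes | no |

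In general t/6 < 1.0 requires t < 6 s, whereas 6/t < 1.0 requires t > 6 s. Every time other than exactly 6 s falls on the wrong side.

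A range check would not readily catch this. Over 4 to 10 s the true speeds run from 0.60 to 1.50 and the written values from 0.67 to 1.67, almost the same span.

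**Change over time.** Improvement from 8 s to 6.5 s:

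- True speed: 6/8 = 0.75 to 6/6.5 = 0.92 m/s, a gain of about 0.17.
- Rule as written: 8/6 = 1.33 to 6.5/6 = 1.08, a fall of 0.25.

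Sign and size both differ. Reversing the sign of an estimate made on t/6 would not recover the speed analysis, because the reciprocal is not linear. A gain of 1 s is a change of −1/6 = −0.17 on the written scale wherever it occurs. In true speed, going from 8 s to 7 s is 0.857 − 0.75 = +0.11 m/s, and going from 5 s to 4 s is 1.50 − 1.20 = +0.30 m/s.

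**The planned test.** The Statistical analysis section specifies a two-way repeated measures ANOVA. Since t/6 is walking time multiplied by the constant 1/6, its F statistics and p-values are identical to those for walking time in seconds. The test would be a test of walking time.

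**Who could be affected at entry.** Table 1 joins its routes by and/or. A past fall, or an FES-I score of at least 20, admits a person whatever their gait speed. Possible sarcopenia itself lists three components, of which gait speed is one. So a person could be misclassified only if entry depends on possible sarcopenia and that status turns on gait speed. The article gives no figures from which to count them.

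**The case against.** The strongest reply is that this is a slip of wording. The sentence names its result as gait speed in m/s, the test is said to assess gait speed, and a cut-off below 1.0 m/s makes sense only if low values mean slow walking. The intended quantity is not in doubt, and nothing in the article shows that any value was computed as t/6. That stands, and it makes every consequence conditional on literal use. It does not make the sentence correct: this is an explicit derivation rule for a listed primary outcome and an eligibility component, and no other text overrides it.

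A reader might go further and infer that the trial has enrolled the wrong people. The article does not support that. It does not show which formula was used at screening, and the fall and FES-I routes bypass gait speed altogether. Nor does it make clear whether the three components of possible sarcopenia must all be met or whether one is enough, so the number affected and the mix of wrongly admitted and wrongly refused people cannot be worked out.

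A reader might also infer that the comparison of TE with CB on this outcome would be invalid. It would not be. A test on t/6 is a sound test of walking time, and the Timed Up and Go, also listed as primary, is itself a timed measure. What would be wrong is the unit, the magnitude and the direction of change.

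**Conclusion.** Wrong as written. The rule yields seconds per metre and labels it m/s.

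Applied literally, it would reverse the gait-speed component for every time other than exactly 6 s, and it would show improvement as loss (0.75 to 0.92 m/s recorded as 1.33 to 1.08). The harm at entry would be confined to people whose inclusion rests on possible sarcopenia through gait speed. On the outcome, the group comparison would remain one of walking time under a wrong label. The sample size of 92 rests on the Timed Up and Go and is untouched.

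The error in the sentence follows from units alone. The consequences rest on the assumption that the rule is used as printed, which the article neither confirms nor excludes.

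**What to change.** Replace the conversion sentence with: gait speed (m/s) = 6 / time in seconds, computed for each attempt and then averaged over the two attempts. The order should be stated because it changes the result slightly. For attempts of 6 s and 8 s, the mean of the two speeds is (1.00 + 0.75) / 2 = 0.875 m/s, while the speed at the mean time is 6/7 = 0.857 m/s.

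Then confirm which formula the screening forms and the dataset use. If they use 6/t, nothing more is needed.

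If t/6 was used, recompute from the recorded times, or invert the stored values. Inversion is exact for values stored attempt by attempt; inverting a stored mean of two attempts gives the speed at the mean time instead. Also re-check the possible-sarcopenia classification of everyone already screened.

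The cost is one sentence and one check. If the inverted rule was in use, there is also a recomputation and a review of screening records for the groups already recruited, and that review would be the larger task. The article does not say whether raw times are kept, so this should be established first.
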